### Trial emulation

#### Data

This study is based on insurance claims data of the German Techniker Krankenkasse (TK). TK is a German statutory health care insurance provider with a market share of approximately 15.3%. In the present study, we will use TK claims data for the years 2021 to 2024 of each individual fulfilling the eligibility criteria in 2022 to 2023 [11].

#### Eligibility criteria

The inclusion criteria for the study require participants to have received at least one psychiatric or psychosomatic treatment^1^ in an inpatient, semi-inpatient, or inpatient equivalent setting between January 2022 to December 2023, under the Psychiatric and Psychosomatic Compensation System (German Akronym: PEPP). In a PEPP number, the first two positions define the structural category, while the subsequent positions offer further specification. Included PEPP structural categories are PO (particularly complex cases), PP (psychosomatics), and PA (psychiatry) for inpatient treatment. For semi-inpatient and inpatient equivalent treatments, the relevant categories are TP and QA (both psychiatry). Not included are the categories for child and youth psychiatry and psychotherapy (codes PK, TK, and QK), in each care setting. Additionally, participants must have reached the age of 18 by the time of the index event. Since a structured DM is required by law we do not include it as an inclusion criterion.

The exclusion criteria for the study are: a previous inpatient or outpatient prescription of sociotherapy within 365 days before the last day of the index event. Additionally, we will exclude individuals who did not maintain continuous insurance coverage throughout the study period including baseline and follow-up period (January 2021– December 2024); employees of TK; individuals who have a registered data protection notice; and those who have explicitly objected to the use of their healthcare records for research purposes.

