## Background

Historically, the German health care system was characterized by a strict division between inpatient and outpatient care, leading to a number of challenges in ensuring the continuity of care for patients following hospitalization [1]. To address these challenges, the German Social Code was amended in 2017 to establish mandatory standards for hospital discharge management (DM) with the aim of improving the transition from inpatient to outpatient care. Under this reform, hospitals are now authorized to prescribe medication, remedies and aids, as well as special services including sociotherapy, home care, specialized outpatient palliative care, digital health applications and transportation services. Hospitals may also certify the incapacity to work if needed and are obliged to provide a discharge document including a medication plan. Since this policy reform was introducedto facilitate the transition from inpatient to outpatient care, the duration of any measures is limited to seven days after discharge. If necessary, the measures may be continued by outpatient providers. Hospitals are mandated to initiate interprofessional discharge planning as early as possible to enhance continuity of care. This paradigm shift in the implementation of DM was enacted through a framework agreement between the National Association of Statutory Health Insurance Funds (GKV), the National Association of Statutory Health Insurance Physicians (KBV) and the German Hospital Federation (DKG) [2].

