### Design

The aim of this study protocol is to describe the emulation of a target trial designed to estimate the causal effect of sociotherapy as a DM measure using observational data from insurance claims records. Following the principles of TTE, we define the hypothetical RCT that we seek to emulate [8, 9]. Based on the primary outcome of interest (30-day readmissions), the sample size for the target trial was calculated. We then provide a detailed description of the TTE using observational data, covering key aspects such as included variables, eligibility criteria, treatment strategies, assignment procedure, follow-up period and outcomes definitions (for a comparison between hypothetical target trial and emulation see Table 1). And finally, we outline the statistical analysis strategy for the TTE.

**Table 1 Tab1:** Target Trial Emulation

	**TARGET TRIAL**	**E2-PSY TRIAL EMULATION**
Eligibily Critera	Inclusion criteria • Adults aged 18 years or over • Patients with a psychiatric treatment in an inpatient, semi-inpatient or inpatient equivalent setting Exclusion criteria • Previous sociotherapy	Inclusion criteria • • Adults aged 18 years or over • Patients with a psychiatric treatment in an inpatient, semi-inpatient or inpatient equivalent setting (PEPP classification PO, PP, PA, TP, or QA) Exclusion criteria • Previous sociotherapy within 365 days before the last day of the index event • No continuous health insurance throughout the study period • Personnal of the insurance provider supplying the data • Existing data protection notice • Existing objection to use of healthcare records for research purposes
Treatment Strategies	Intervention group • Prescription of sociotherapy as acomponents of discharge management (last day of the index event) Control group • No prescription of sociotherapy as a componentof discharge management (last day of the index event)	Intervention group • Prescription of sociotherapy as a components of discharge management (last day of the index event) Control group • No prescription of sociotherapy as a component of discharge management (last day of the index event)
Assignment procedures	Participants will be randomly assigned to either treatment armon the last day of the index event. Patients will be aware of the treatment armthey have been assigned to	Quasi-randomization will be archived through a propensity score-based method, either propensity score matching or inverse probability weighting

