### Treatment strategies

#### Intervention group

The intervention group receives a prescription for sociotherapy as a component of the structured DM.

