#### Control group

The control group receives standard care, which includes regular DM following psychiatric treatment but does not involve a prescription for sociotherapy.

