### Follow-up period

We follow up with participants for 30 days after discharge to assess the primary outcome, and for up to 365 days for secondary outcomes, or until death—whichever occurs first. During the follow-up period, we will evaluate the continuation of sociotherapy prescriptions as a component of a structured DM, as well as any new prescriptions issued in the outpatient setting.

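### Discharge management is assumed from the legal duty, so patients who left against advice or were transferred out of psychiatric care can enter, mainly as controls, without having received the stated control strategy

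*Protocol article*

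**What the plan says.** Under Eligibility criteria, the article includes adults with at least one psychiatric or psychosomatic treatment in the listed PEPP categories in 2022–2023. On DM it states: "Since a structured DM is required by law we do not include it as an inclusion criterion". The legal duty is the only reason given. The Background describes that duty as binding requirements placed on hospitals since 2017; it does not say that every stay ends with DM delivered.

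Both treatment strategies presuppose DM. For the intervention: "The intervention group receives a prescription for sociotherapy as a component of the structured DM". For the comparator: "The control group receives standard care, which includes regular DM following psychiatric treatment but does not involve a prescription for sociotherapy". In the target-trial column of Table 1, assignment is placed at the end of the stay: "Participants will be randomly assigned to either treatment armon the last day of the index event".

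The Confounders section and Table 2 list PEPP category, length of the index event, diagnoses, intensive treatment, emergency admission, eight other DM measures, medical history and sociodemographic variables. Discharge reason is not listed.

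Two further rules limit the point. Eligibility criteria will "exclude individuals who did not maintain continuous insurance coverage throughout the study period including baseline and follow-up period", that is, January 2021 to December 2024. The Outcomes section treats a same-day transfer between inpatient, semi-inpatient and inpatient-equivalent settings as part of the index event.

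**The concern.** The data rule for controls does not implement the control strategy that the article defines. A patient holding a DM prescription of sociotherapy has had DM. A patient without one may have had regular DM with no sociotherapy, which is the intended comparator, or no DM at all. The eligibility rule cannot tell these apart.

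The patients most likely to have had no regular DM are those who left against advice and those moved to a somatic ward or another institution. They would rarely hold a sociotherapy prescription, so they gather in the control arm. Their 30-day psychiatric readmission risk may differ from that of regularly discharged controls for reasons unrelated to sociotherapy. If early leavers return sooner, sociotherapy looks protective. If transferred patients are for a time not at risk of psychiatric readmission, it looks harmful.

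The planned adjustment can remove only what its variables capture. A regular discharge with no other prescriptions looks the same in Table 2 as a discharge with no DM.

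**Working it through.** **Passages side by side**

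| Element | Intervention | Control |
|---|---|---|
| Strategy as defined | Prescription as part of DM | Regular DM, no such prescription |
| What the data rule requires | DM prescription present | Qualifying stay, prescription absent |
| DM guaranteed by the data rule? | Yes | No |

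The groups that might fall into the gap:

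- Left against advice: no eligibility rule or covariate addresses them.
- Transferred outside the included psychiatric settings: not addressed.
- Same-day transfer between included settings: handled under Outcomes as a continuation of the index event.
- Died during the index stay: removed by the coverage rule, read literally.

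**Plan's own figures**

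The article gives no share of irregular discharges and no readmission rate for them. Its only related figures are N = 449 at a 10% baseline rate and N = 329 at 20%, for an effect size of 0.3 whose metric is not named in the text. These can be reproduced by reading 0.3 as a shift on the probit scale, with two-sided 5% alpha, 80% power, 1:1 allocation and a pooled-variance test of two proportions (all but the power are assumptions):

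- 10% against Φ(z(0.10) + 0.3) = 16.3% gives 449 per arm.
- 20% against Φ(z(0.20) + 0.3) = 29.4% gives 329 per arm.

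The present point changes neither figure. The same shift as a reduction is 10% to 5.7%, or 4.3 percentage points, which is used below only as a yardstick.

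**Illustration of size**

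All inputs except the baseline rates are assumptions. Let p be the 30-day readmission rate in the treated and in regularly discharged controls (no true effect), f the share of controls without regular discharge, and k their risk relative to the other controls. Nothing is removed by adjustment.

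- Control rate: c = p × [1 + f × (k − 1)]
- Apparent RR: p / c = 1 / [1 + f × (k − 1)], whatever the baseline
- Apparent OR: [p / (1 − p)] / [c / (1 − c)]

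At p = 10%:

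| f | k | c | Shift (points) | RR | OR |
|---|---|---|---|---|---|
| 2% | 1.5 | 10.1% | +0.1 | 0.99 | 0.99 |
| 5% | 2 | 10.5% | +0.5 | 0.95 | 0.95 |
| 10% | 3 | 12.0% | +2.0 | 0.83 | 0.82 |
| 15% | 3 | 13.0% | +3.0 | 0.77 | 0.74 |
| 2% | 0 | 9.8% | −0.2 | 1.02 | 1.02 |
| 10% | 0 | 9.0% | −1.0 | 1.11 | 1.12 |

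The rows with k = 0 stand for patients who cannot be readmitted within the window. At p = 20%, f from 2% to 10% with k from 1.5 to 3 gives an OR of 0.99 to 0.79; with k = 0 the OR is 1.03 to 1.14.

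**Effect of partial adjustment**

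If the listed covariates removed half of the excess risk in the most extreme row, k would fall from 3 to 2 and the RR would be 1 / (1 + 0.15 × 1) = 0.87. If they removed three quarters, k = 1.5 and the RR would be 1 / (1 + 0.15 × 0.5) = 0.93.

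**The case against.** The strongest defence is that this is a disclosed choice with a reason, and that the emulation matches its target trial as written. The target-trial column of Table 1 asks for age and psychiatric treatment, excludes previous sociotherapy, and sets no criterion on DM or type of discharge. That stands: a reader might infer that the target trial would randomise none of these patients, and the document does not say so. The mismatch is with the control strategy, not with a stated eligibility rule.

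A reader might also infer four stronger claims that the document does not support.

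- *Deaths in hospital inflate the control arm.* A patient who died during a 2022–2023 stay cannot have coverage to December 2024, so the coverage rule, read literally, removes them. What remains is a tension within the article, because Table 1 and Follow-up period let follow-up run "or until death—whichever occurs first", which could not happen before December 2024 under that rule.
- *All transfers are affected.* Same-day transfers between included settings continue the index event.
- *These patients could never have been prescribed sociotherapy.* The Background says that discharge planning starts as early as possible, so a prescription might exist before an unplanned departure. "Predominantly controls" is as far as one can go.
- *The bias is known to favour sociotherapy.* The shares and risks above are assumed, the two groups may pull in opposite directions, and the calculation makes no allowance for adjustment. Length of stay, emergency admission, diagnoses, previous psychiatric hospital days and other DM measures would plausibly absorb part of it.

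Finally, a condensed article may leave details of the index discharge to a fuller document. That would answer a point about missing detail. Here the article states the decision and rests it on the legal duty alone.

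**Conclusion.** The point holds in a limited form. The plan presumes delivery of DM from a legal duty, defines the comparator as including DM, and neither selects nor adjusts on mode of discharge. Controls who left against advice or were transferred outside the included settings can be analysed as if they had received the comparator.

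The size and net direction cannot be derived from the document. Under the assumed 2–15% share and 1.5–3 times the risk, before adjustment and at a 10% baseline, the spurious shift is 0.1 to 3.0 points, from negligible (OR about 0.99) to an RR of about 0.77 in favour of sociotherapy. Against the 4.3-point yardstick, the upper end would be a substantial part of the effect sought. Patients not at risk of readmission would move the estimate the other way. This is a comparability gap worth closing because closing it is cheap, not a demonstrated bias.

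**What to change.** If the hospital claims hold the discharge reason (an assumption; the article mentions only the reason for admission), restrict eligible index events in both arms to regular discharges at time zero, and state the same criterion in the target-trial column of Table 1. If the broader population is preferred, add discharge reason to the propensity score and to the outcome models, and report the restricted population as a sensitivity analysis. In either case, replace the legal-duty sentence with a description of how the data identify the stated control strategy, and report the number of non-regular discharges by arm.

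Separately, reconcile the coverage requirement to December 2024 with the rule that follow-up ends at death, so that it is clear whether patients who die are excluded or censored.

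The cost is one filter or one covariate from the same claims. The downsides are a somewhat smaller control pool and conclusions limited to patients discharged regularly. If the discharge reason is not available, the gap should be named as a limitation in the Discussion, which currently lists only social determinants such as social support, family and employment status as uncontrolled.

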Follow-Up Period	Starts at randomization and ends 30 days/365 days after discharge of the index event, death, or loss to follow-up	Starts at the last day of the index event and ends 30 days/365 days after discharge of the index event, death, or loss to follow-up
Outcome	Primary outcome • Readmission to hospital for psychiatric treatment within 30 days after discharge Secondary outcomes • Readmission to hospital for psychiatric treatment within 365 days after discharge • Time to first psychiatric rehospitalization • Total number of rehospitalizations within 365 days after discharge • Cumulative number of days spent in the hospital due to psychiatric admissions during 365 days after discharge	Primary outcome • Readmission to hospital for psychiatric treatment within 30 days after discharge Secondary outcomes • Readmission to hospital for psychiatric treatment within 365 days after discharge • Time to first psychiatric rehospitalization • Total number of rehospitalizations within 365 days after discharge • Cumulative number of days spent in the hospital due to psychiatric admissions during 365 days after discharge
Causal Contrasts Of Interest	• Intention-To-Treat (ITT): The ITT evaluates the average treatment effect among the treated (ATT), regardless of whether the patients adhered to the treatment • Per-Protocol (PPA): The PPA evaluates the average treatment effect among the treated (ATT), accounting for the non-adherence to the sociotherapy treatment in the intervention group, and usage of sociotherapy in the control group due to prescriptions of sociotherapy unrelated to the assignment procedure	• Intention-To-Treat (ITT): The ITT evaluates the average treatment effect among the treated (ATT), regardless of whether the patients adhered to the treatment • Per-Protocol (PPA): The PPA evaluates the average treatment effect among the treated (ATT), accounting for the non-adherence to the sociotherapy treatment in the intervention group, and usage of sociotherapy in the control group due to prescriptions of sociotherapy unrelated to the assignment procedure

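### The insurance-coverage rule running to December 2024 makes eligibility depend on events after discharge and does not fit the stated ends of follow-up

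*Protocol article*

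**What the plan says.** The Eligibility criteria section of the protocol article states that the authors will "exclude individuals who did not maintain continuous insurance coverage throughout the study period including baseline and follow-up period", and gives that period in brackets as January 2021 to December 2024. The emulation column of Table 1 repeats this as "No continuous health insurance throughout the study period". The target trial column has no coverage or survival condition. Its only entry is "Exclusion criteria • Previous sociotherapy".

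Qualifying treatment is that received "in an inpatient, semi-inpatient, or inpatient equivalent setting between January 2022 to December 2023". The Data section matches this: "we will use TK claims data for the years 2021 to 2024 of each individual fulfilling the eligibility criteria in 2022 to 2023".

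Both columns of Table 1 give a follow-up that "ends 30 days/365 days after discharge of the index event, death, or loss to follow-up". In the emulation it starts on the last day of the index event. The Follow-up period section gives 30 days for the primary outcome and up to 365 days for the secondary outcomes, "or until death—whichever occurs first". It does not mention loss to follow-up.

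**The concern.** A trial can apply at randomization only criteria that are known at randomization. Whether a patient will still be insured in December 2024 is not known on the day of discharge, so the emulation uses a criterion that its own target trial could not use. Avoiding such conditioning on the future is a main reason for choosing target trial emulation.

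Three things are at stake.

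- **Population.** The stated contrast is the effect among the treated. Under the rule it becomes the effect among treated patients who stayed with the insurer to a fixed calendar date and, on the literal reading, survived to it.
- **Bias.** If leaving or dying after discharge is related both to the prescription and to readmission, the selected groups are no longer comparable. A propensity score built on baseline variables does not repair selection on later events. The Discussion lists unmeasured social factors as a limitation but not this selection.
- **Sample.** The rule drops patients whose outcome data are complete, while the Sample size calculation section says the emulation will be discontinued if the required number is not reached.

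**Working it through.** The plan states no figure for this point, so there is none to reproduce. The check is date arithmetic on the plan's own windows, followed by an illustration on assumed rates.

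**1. Coverage required after discharge.** Inputs: coverage end 31 December 2024 (Eligibility criteria); outcome windows 30 and 365 days (Table 1); discharge dates taken to lie in the index window, 1 January 2022 to 31 December 2023.

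| Discharge | Days to 31 Dec 2024 | Beyond day 30 | Beyond day 365 |
|---|---|---|---|
| 1 Jan 2022 | 1,095 | 1,065 | 730 |
| 31 Dec 2022 | 731 | 701 | 366 |
| 31 Dec 2023 | 366 | 336 | 1 |

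The required period differs about threefold (1,095 / 366 = 3.0) by calendar date alone.

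**2. Coverage required beforehand.** From 1 January 2021 it is 365 days to 1 January 2022 and 1,094 days to 31 December 2023. The look-back actually used is 365 days for previous sociotherapy (Eligibility criteria) and twelve months for comorbidity and psychiatric hospital days (Table 2).

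**3. Consistency with the follow-up rules.** A patient who leaves the insurer within 365 days of discharge does so before 31 December 2024 and is excluded. Loss by leaving the insurer therefore cannot occur in the analysed cohort, although Table 1 lists loss as an end of follow-up. If death also breaks continuity, nobody in the cohort can die during follow-up, although Table 1 and the Follow-up period section both end follow-up at death.

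**4. Illustration of size.** The article gives no rates of death or of leaving. Assume a constant combined annual exit probability h of 2%, 4% or 6%, with death counted as a break in coverage.

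- Incomplete at day 30: 1 − (1 − h)^(30/365)
- Incomplete at day 365: h
- Excluded, discharge at the start of 2022 (three years): 1 − (1 − h)^3
- Excluded, cohort average: with index dates spread evenly, the required period runs from about one to three years with mean two, so 1 − (1 − h)^2

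| h | Incomplete at day 30 | Incomplete at day 365 | Excluded, average | Excluded, early 2022 |
|---|---|---|---|---|
| 2% | 0.17% | 2% | 4.0% | 5.9% |
| 4% | 0.33% | 4% | 7.8% | 11.5% |
| 6% | 0.51% | 6% | 11.6% | 16.9% |

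On these assumptions about half of the average exclusions (for h = 4%, 7.8 − 4 = 3.8 points) concern patients with a complete 365-day record. Nearly all (7.8 − 0.3 = 7.5 points) concern patients with a complete 30-day record.

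**The case against.** The strongest defence reads the rule together with the follow-up definition. Coverage is required through baseline and follow-up, and follow-up ends at death. A patient insured until death was then covered throughout and stays in. The Follow-up period section fits this, since it names death and omits loss. The dates can also be read as the outer frame of the study: one year before the earliest index to one year after the latest, which is the data extract. On that reading each patient needs only their own baseline year and 365 days.

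Part of this stands. A reader might infer that the rule removes every death. That holds only if death breaks continuity, and the article says neither that it does nor that it does not. A reader might also take the early-2022 figures of 6% / 12% / 17% as the loss for the whole cohort; they are the extreme, on assumed rates. An end-of-follow-up clause that never takes effect is also redundant rather than logically opposed to the rule.

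The defence does not remove the problem. The wording refers to the whole study period with explicit dates, which favours one calendar window for everyone. Even on the lenient reading, leaving the insurer within a year of discharge excludes a patient through post-discharge information. Someone who leaves between day 31 and day 365 is still dropped from a 30-day outcome that was fully observed. The loss clause in Table 1 still has nobody to whom it could apply through leaving the insurer.

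It might further be inferred that the 30-day result is biased, or that scarce treated patients are being lost. The article supports neither: it gives no exit rates by group and does not say how common the prescription is.

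**Conclusion.** The point holds in this form: the coverage rule makes eligibility depend on events after time zero, departs from the target trial column, and does not fit follow-up ending at death or loss. Selection on staying with the insurer follows from the rule on any reading. Selection on survival follows only if coverage until death is not counted as continuous.

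The dates are firm if the rule is read as written: 366 to 1,095 days of later coverage, and up to 1,094 days of earlier coverage against a 365-day look-back. The percentages (about 4% / 8% / 12% excluded on average) are illustrative. They rest on assumed exit of 2% / 4% / 6% per year, a constant rate, evenly spread index dates and death counted as exit. The direction and size of bias cannot be derived from the article. Few patients leave or die within 30 days on these assumptions, and bias in the primary result may be small.

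**What to change.** Replace the criterion, in the Eligibility criteria section and in Table 1, with continuous insurance from 365 days before index admission to the last day of the index event. Keep patients who later die or leave. End each patient's follow-up at day 30 or 365, death, or end of insurance, and use the same wording in Table 1 and in the Follow-up period section. Handle end of insurance as censoring and death as a competing event, and use person-time as an offset in the count models. The detail, such as how censoring enters the 365-day binary outcome, can sit in the analysis plan.

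The 2021 to 2024 extract supports this for index admissions from 1 January 2022. An earlier admission that ends inside the window would lack the full look-back, so the text should say how such cases are treated.

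The cost is one changed extraction criterion, modest extra analysis work, and slightly incomplete follow-up for a few percent of patients. If the authors keep a coverage requirement after discharge, they should at least state whether it applies per patient and whether death counts as a break, and list the selection as a limitation.
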